### Sample size

25 per group will provide sufficient information for planning the proposed subsequent main randomised trial with an anticipated standardised effect size of about 0.2 on the primary outcome, handgrip strength [46]. Considering a 20% attrition rate [47], the sample size of this pilot RCT has been calculated as 25 × (1 + 20%) = 30 in each group.

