### Allocation and blinding

After they give their informed consent, eligible participants will be randomised into the intervention group (IG) or the control group (CG) with a 1:1 ratio. Block randomisation with a block size of 4 will be used to balance the numbers in each group. Three research assistants who will not otherwise be involved in this study will perform the randomisation independently to ensure allocation concealment and avoid selection bias. The random numbers will be generated by a computer and sealed in opaque envelopes and delivered to each participant.

Due to the characteristics of the interventions (the MBPE vs health education), it will be impossible to blind the participants and interventionists. The following personnel will, however, be blinded: the research assistants recruiting participants, the research assistants performing randomisation and the outcome assessor.

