6	Understanding habitual thinking patterns during life and PE	Help participants to understand that behaviour, thoughts and feelings are interwoven, and learn to notice the tendency to label things during PE	1) Mini lectures on becoming unstuck and having a flexible mind: using common negative feelings of older adults with sarcopenia to show how these negative feelings stick in the mind, behaviour, etc. 2) Mindful practice: 7-min sitting meditation 3) Tips on observing the tendency to label things during PE	**PE movement** Same as Week 1 **PE intensity** Same as Week 5
7	Self-compassion during life and PE	Help participants to understand self-compassion, how to improve self-compassion and show more appreciation towards PE and life	1) Mini lectures on compassion vs criticism and nourishing vs depleting activities 2) Mindful practice: 7-min loving meditation 3) Tips on self-compassion during PE	**PE movement** Same as Week 1 **PE intensity** Same as Week 5
8	Mindfulness-based PE and mindfulness in life	Help participants to learn to integrate mindfulness and MBPE into daily life and to view things from a beginner’s perspective	1) Mini lecture on incorporating mindfulness and mindfulness-based PE into daily life: what informal mindfulness activities we can do in daily life; when, where and how to do formal mindfulness practice, etc. 2) Mini lecture on keeping a beginner’s mindset: its importance and how to re-view the things that we ignore or take for granted 3) Mindful practice: 7-min sitting meditation with life nourishment	**PE movement** Same as Week 1 **PE intensity** Same as Week 5

MBI, Mindfulness-Based Intervention; MBPE, Mindfulness-Based Physical Exercise; PE, Physical Exercise.

To facilitate the participants’ learning, the face-to-face sessions will be provided in the first four weeks under the supervision of a qualified mindfulness therapist and a qualified sports coach in small groups of 6–10 participants to ensure adequate supervision at the CHCC [55]. Then, the intervention sessions will gradually transition to hybrid mode during weeks 5–12. Specifically, the participants will attend the face-to-face sessions once a week in weeks 5–8 and once every two weeks in weeks 9–12. To achieve a session frequency of twice a week, in addition to the sessions at the CHCC, the participants will perform the interventions at home using videos and templates containing the MBIs and PE components of our MBPE intervention.

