#### 2. Health education in the CG

The aim of the CG will be to avoid the influence of socialisation and interaction with others on the participants’ motivation to perform PE and thus isolate the effectiveness of the MBPE program. Thus, health education consisting of discussions provided by a registered nurse will be conducted. The number of sessions, duration, frequency, group size and delivery modality of the CG will be similar to those of the IG. The topics of this health education will be the prevention and management of common diseases among older adults, such as hypertension and diabetes, and will not include MBI or PE.

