### Statistical analysis

#### 1. Quantitative data analysis

IBM SPSS 23.0 will be used to statistically analyse the data. For continuous variables, the Shapiro–Wilk test will used to evaluate normality. Mean and standard deviation (SD) will used to describe normally distributed data, especially the outcomes to provide information for calculation of standards effect sizes of the subsequent RCT; otherwise, median, interquartile range (P_25_, P_75_) and range (minimum, maximum) will be used.

For continuous variables, an independent-samples *t* test will be used if the data are normally distributed; otherwise, the Mann–Whitney *U* test will be used. Chi-square or Fisher’s tests will be used for categorical data. Feasibility and acceptability will be presented in terms of rate or absolute number based on the nature of the data. The generalised estimating equation model will be used to analyse the preliminary effects of this study. The standardised mean difference with corresponding 95% confidence intervals will be presented to describe the mean differences of both primary and secondary outcomes between the intervention group and the control group [70]. All data analyses will be conducted with two-tailed tests with a significance level of p < 0.05. Both per-protocol (PP) and intention-to-treat analysis will be conducted. The attention rate >80% will be included in the PP analysis.

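### Both arms are delivered in small groups, but the stated analysis takes no account of delivery group, so intervals for the secondary effects are too narrow if within-group correlation is positive

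*Protocol article*

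**What the plan says.** The Protocol article randomises individuals: "eligible participants will be randomised into the intervention group (IG) or the control group (CG) with a 1:1 ratio" (Allocation and blinding).

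Delivery is in groups. For the first four weeks the intervention is given face to face "in small groups of 6–10 participants to ensure adequate supervision at the CHCC" (The MBPE intervention in the IG). After that it becomes hybrid: "the participants will attend the face-to-face sessions once a week in weeks 5–8 and once every two weeks in weeks 9–12", with the remaining sessions done at home. For the control arm, "The number of sessions, duration, frequency, group size and delivery modality of the CG will be similar to those of the IG" (Health education in the CG).

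The Sample size section states that "25 per group will provide sufficient information for planning the proposed subsequent main randomised trial with an anticipated standardised effect size of about 0.2", with handgrip strength as the outcome, and that "the sample size of this pilot RCT has been calculated as 25 × (1 + 20%) = 30 in each group".

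The Quantitative data analysis section lists the independent-samples t test or Mann–Whitney U for continuous variables, and then says: "The generalised estimating equation model will be used to analyse the preliminary effects of this study". It also promises standardised mean differences with 95% CIs and two-sided tests at 0.05. The planning inputs it names for the later trial are means and SDs for effect sizes. Outcomes are measured twice, at baseline and straight after the intervention. Delivery group, an ICC or a design effect appears in neither the sample-size nor the analysis text.

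**The concern.** People who train and talk together in the same small group may end up more alike than people in different groups. The article gives a reason to expect this for motivation: it builds the control arm to offset the effect of socialising and interaction on willingness to exercise. A matched control balances the average effect of being in a group. It does not remove variation between groups, and that variation is what inflates the variance of the arm comparison.

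A t test or Mann–Whitney U treats participants as independent. A GEE for two measurements per person, specified in the usual way, clusters on the person and not on the delivery group. If within-group correlation is positive, both understate the standard error.

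Two things are at stake. One is the CIs and p values for the secondary effect outcomes. The other is the set of planning quantities passed to the main trial, which is incomplete for a group-delivered intervention if it holds only an SD and an effect size.

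**Working it through.** **Inputs from the Protocol article**
- Group size m: 6–10 in the intervention arm. The control arm is described as similar; the range is not repeated there.
- Randomised per arm: 25 × (1 + 0.20) = 30, which reproduces the stated size. The plan's own target for analysis is 25 per arm.
- Two-sided significance level: 0.05. Standardised effect for the main trial: about 0.2.

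**Assumed, because the article does not give them:** an ICC from 0 to 0.10, equal in both arms, and 80% power for the main trial.

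**Groups and sessions**
- Groups per arm: 30/10 = 3 to 30/6 = 5, so about 6–10 groups in total.
- Face-to-face sessions: 4 × 2 + 4 × 1 + 2 = 14 of 24. The other 10 are at home. Groups of 6–10 are explicit only for the first 8 of the 14.

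**Formulas**
- Design effect: DE = 1 + (m − 1) × ICC.
- Correct CI width relative to the independence width: √DE.
- Actual two-sided error of a nominal 5% test: 2 × P(Z > 1.96/√DE). This is a normal approximation.

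**Full groups, m = 6 to 10**

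| Assumed ICC | DE | CI width multiplier | Actual type I error |
|---|---|---|---|
| 0 | 1.00 | 1.00 | 5.0% |
| 0.01 | 1.05–1.09 | 1.02–1.04 | 5.6–6.0% |
| 0.05 | 1.25–1.45 | 1.12–1.20 | 8.0–10.4% |
| 0.10 | 1.50–1.90 | 1.22–1.38 | 11.0–15.5% |

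**After attrition, 25 of 30 analysed per arm**
- Group size: 6 × 25/30 = 5 to 10 × 25/30 = 8.3.
- DE at ICC 0.05: 1 + 4 × 0.05 = 1.20 to 1 + 7.33 × 0.05 = 1.37. Type I error is about 7–9%.
- Half-width of the 95% CI for the standardised mean difference under independence: 1.96 × √(2/25) = 0.55. With these design effects: 1.96 × √(2 × 1.20/25) = 0.61 to 1.96 × √(2 × 1.37/25) = 0.65.

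**What the ICC would mean for a main trial** (illustration only; the article contains no such calculation)
- At d = 0.2, two-sided 0.05 and 80% power, the unclustered size is 393 per arm.
- ICC 0.01: 393 × 1.05 = 413 to 393 × 1.09 = 429 per arm. Staying at 393 gives 78–77% power.
- ICC 0.05: 393 × 1.25 = 492 to 393 × 1.45 = 570 per arm. Staying at 393 gives 71–64% power.

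**The case against.** The strongest reply is that the article never says participants are treated as independent in the effect model. A reader might infer that the GEE clusters on the person only. That is the ordinary specification with two time points, but the cluster unit is not stated and a full protocol or SAP may give it. This stands as a limit on the wording. The t test and Mann–Whitney U do assume independence, although the article lists them generically and does not say that they are the effect analysis. If they serve baseline comparisons only, group delivery cannot affect them, because baseline precedes any session.

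A reader might also infer that the main trial will be planned without a design effect. The article contains no main-trial calculation. It names means, SDs and effect sizes as planning inputs, which does not rule out an allowance for clustering.

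The mechanism can be overstated too. Fixed group membership is not stated, and 10 sessions are at home, so any correlation may be diluted. If the same therapist, coach or nurse leads every group in an arm, leaders add no between-group variance within that arm. Peers and discussion still can.

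Finally, the consequence is limited. Feasibility and acceptability are the primary outcomes and are presented as rates or numbers. The effects are labelled preliminary, and the article says a full trial is needed to test effectiveness. An ICC from this pilot would also be weak: with about 8 groups of 7.5 and a true ICC of 0.05, its standard error is about 0.10. All of this is fair. It reduces the size of the point and shapes the remedy, but leaves delivery group absent from the stated analysis.

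**Conclusion.** The point holds in conditional form. Both arms are group-delivered and no stated analysis or sample-size step takes account of it. The intervals and p values for the secondary effects are too narrow if within-group correlation is positive. The loss is nil at ICC 0, trivial at 0.01, and noticeable at 0.05, where it is somewhat smaller once attrition shrinks the groups. These figures rest on an assumed ICC, equal in both arms, on stable groups of the stated size, and on a GEE clustered on the person.

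The documents do not support the stronger reading that the intervals are too narrow outright, or that the main trial is bound to be undersized. The first needs an ICC that the article does not give, and the second needs a calculation that it does not contain. The estimates of the primary feasibility and acceptability rates are not affected. This is a cheap improvement to the secondary analysis and to the planning inputs, not a flaw in the trial's main purpose.

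**What to change.** 1. Record the session-group identifier for every participant in both arms, and any change of group. It may not be recoverable later.
2. State the clustering unit of the GEE. Analyse the effect outcomes, at least as a sensitivity analysis, with a random intercept for delivery group within arm and small-sample degrees of freedom such as Satterthwaite. With about 6–10 groups in total, an uncorrected sandwich variance clustered on group would be unreliable.
3. Report the ICC with its interval, for example for handgrip strength and motivation, and label it as imprecise.
4. State that the main-trial sample size will apply a design effect over a range of ICCs and will not rely on the pilot SD and effect size alone.

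The cost is one extra variable and a few sentences of analysis text. The downside is wider intervals and an ICC too imprecise to use as a single planning value.

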#### 2. Health education in the CG

The aim of the CG will be to avoid the influence of socialisation and interaction with others on the participants’ motivation to perform PE and thus isolate the effectiveness of the MBPE program. Thus, health education consisting of discussions provided by a registered nurse will be conducted. The number of sessions, duration, frequency, group size and delivery modality of the CG will be similar to those of the IG. The topics of this health education will be the prevention and management of common diseases among older adults, such as hypertension and diabetes, and will not include MBI or PE.

### Primary outcomes and measures

The primary outcomes of this pilot RCT will be the feasibility and acceptability of the MBPE intervention.

#### 1. Feasibility of the MBPE intervention

Feasibility will be evaluated using the time spent recruiting participants, the eligibility rate (number of eligible participants / number of screened participants) and the recruitment rate (number of participants recruited / number of eligible participants).

#### 2. Acceptability of the MBPE program

Acceptability will be evaluated using the prospective acceptability, the concurrent acceptability and the retrospective acceptability [56]. Prospective acceptability will be measured as the recruitment rate and the reasons for which older adults did not get involved in the program[56]. Concurrent acceptability will be assessed using the attendance rate (sessions attended by the participants / all sessions), completion rate (sessions in which participants were actually involved and at least 80% completed / all attended sessions), attrition rate (number of participants dropping out / total number of participants) and the reasons for discontinuing [56]. Attrition will be considered if the completion rate is less than 80%. To have a depth exploration of the participants’ experience and avoid leaking privacy, individual interviews will be used to measure the retrospective acceptability, the detailed guideline in Table 3. The individual interviews will be conducted by two researchers who both have experience in individual interviewing and are familiar with sarcopenia and mindfulness. Purposive sampling will be used, and the sample size will depend on the data duration. Reflective journals written by the interviewers will be used to avoid bias and ensure the transparency of the research process [57]. With the participants’ consent, the individual interviews will be carried out face-to-face and audio recorded.

**Table 3 pone.0302235.t003:** Guide to individual interviewing of participants in intervention group.

Number	Questions
**Q1**	**Generally, what do you think of this intervention?**

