### Intervention description

#### 1. The MBPE intervention in the IG

The MBPE intervention aims to help participants learn mindfulness and maintain the state of mindful during PE to improve their experiences of PE and motivation to perform PE [27, 38]. Each session will last for approximately 60 min and have a concrete theme, learning objectives and corresponding activities, including a 5–10-min introduction, 20-min MBI, 30-min PE and 5–10-min sharing and discussion [49, 51, 52]; details are provided in Table 2. The contents and activities of the MBI components will be adapted to the theme of each session, whereas the PE movements will be the same throughout the program but with increased intensity every two weeks until a moderate intensity (measured using the Borg scale) is achieved [50]. The MBPE intervention will be conducted twice a week for 12 weeks [19]. The content of week 8 will be repeated in weeks 9–12 to enhance the benefits of MBPE and help the participants incorporate MBPE into their daily lives, given that they are expected to be able to learn the MBI within 8 weeks [54]. To better combine the MBI and PE components, tips on remaining mindful during PE will be given to the participants.

**Table 2 pone.0302235.t002:** Themes, mindfulness and PE components in the MBPE intervention.

Week	Theme of each session	Objectives	MBI component (20 min)	PE component (40 min)
1	Introduction to MBPE	Help participants to understand mindfulness, MBPE and key points of keeping mindful	1) Mini lectures on mindfulness, MBPE and key points of remaining mindful during PE 2) Initial experience of mindfulness (3-min breath meditation)	**PE movement** 1) Warm up (10 min): mindful torso rotation, mindful shoulder rotation, mindful wrist wrap, mindful knee circles, mindful ankle rotation 2) RE (20 min): mindful lateral hand raises, mindful hip abduction, mindful bicep flexors, mindful straight leg lift, mindful handgrip strength exercise, mindful toes up, mindful heels up 3) Cool down (10 min): mindful bicep stretch, mindful tricep stretch, mindful calf stretch, mindful quadricep stretch, mindful cross-legged twist, mindful back stretch **PE intensity** 1) Fairly light (10–11 on Borg scale) 2) 2 sets, 8–10 repeats

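### Attrition, part of a primary outcome, has two unreconciled definitions, and the 80% completion rule can label participants who stayed to the end as attrition

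*Protocol article*

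**What the plan says.** Under Primary outcomes and measures, the article states: "The primary outcomes of this pilot RCT will be the feasibility and acceptability of the MBPE intervention". The Abstract lists the attrition rate among the acceptability measures.

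The section on acceptability of the MBPE program then gives three rates and one rule:

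- Attendance: "attendance rate (sessions attended by the participants / all sessions".
- Completion: "completion rate (sessions in which participants were actually involved and at least 80% completed / all attended sessions".
- Attrition: "attrition rate (number of participants dropping out / total number of participants".
- The rule: "Attrition will be considered if the completion rate is less than 80" per cent.

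The section also collects reasons for discontinuing. It does not define dropping out in any other way, and it does not say whether the 80% rule replaces, interprets or adds to the dropout count.

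The Sample size section uses the same word for planning: "Considering a 20% attrition rate [47], the sample size of this pilot RCT has been calculated as 25 × (1 + 20%) = 30 in each group".

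**The concern.** Dropping out concerns whether a person remains in the trial. Completion, as defined here, concerns how much of a session a person does once there. Its denominator leaves out missed sessions, and withdrawal or a missing final assessment has no bearing on it. Using it to decide attrition joins two separate quantities under one label.

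The allowance in the Sample size section raises 25 to 30 per group. That makes sense only if attrition there means participants lost from the number needed. The section does not define the word, so this is an inference, but it is the natural one. An attrition rate driven by the 80% rule would not measure that loss. The pilot could then neither check its own 20% assumption nor give the planned main trial a clear retention figure.

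**Working it through.** **Inputs**

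- Sessions: "The MBPE intervention will be conducted twice a week for 12 weeks", so 2 × 12 = 24.
- Attendance = attended / 24. Completion = sessions at least 80% completed / sessions attended. The rule flags attrition if completion < 0.80. All are from the acceptability section.
- Planned allowance: 20%, from the Sample size section.

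**The plan's own figure.** 25 × (1 + 0.20) = 30 per group, as stated. It is reproduced here only to show how attrition is used in planning; the inflation formula is not at issue in this point.

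**The rule applied to single participants**

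| Participant | Attended | Completed | Attendance | Completion | 80% rule |
|---|---|---|---|---|---|
| Stays throughout, assessed at end | 24 | 19 | 100% | 19/24 = 79.2% | attrition |
| Stays throughout, assessed at end | 24 | 20 | 100% | 20/24 = 83.3% | not attrition |
| Stops after week 4 | 8 | 8 | 8/24 = 33.3% | 8/8 = 100% | not attrition |
| Stops halfway | 12 | 12 | 12/24 = 50% | 12/12 = 100% | not attrition |
| Never attends | 0 | 0 | 0% | 0/0 | undefined |

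The first row follows from the sentence as written, whether the rule stands alone or is added to ordinary dropout. The last three rows are a problem only if the rule is the operational criterion for dropping out.

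**The readings applied to one arm (assumed mix, for illustration).** Of 30 participants, 10 withdraw after week 4 with all 8 sessions completed and no final assessment, 3 attend all 24 with 19 completed, and 17 attend and complete everything.

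- Dropout formula alone: 10/30 = 33.3%.
- 80% rule alone: 3/30 = 10.0%, and none of the three had left.
- Both added together: (10 + 3)/30 = 43.3%.

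**The direction is not fixed.** Take 20% of 30 = 6 leavers, each having completed every session attended, and assume 6 full attenders at 19/24. The 80% rule alone gives 6/30 = 20%, the same as the true loss of 6/30 = 20%, but it flags six entirely different people. Adding the two gives 12/30 = 40%.

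**Would a different completion denominator repair it?** Over all 24 sessions, the person who stops after week 4 has 8/24 = 33.3% and is caught, and the never-attender has 0/24 = 0%. The full attender remains at 19/24 = 79.2% and is still attrition. In the first arm this gives 13/30 = 43.3%. The denominator is therefore not the core fault. The fault is deciding attrition by completion at all.

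**The case against.** The strongest reply is that the rule says *if*, not *only if*. The formula already counts participants who drop out, and reasons for discontinuing are recorded, so the 80% sentence may be an extra trigger. This stands. A reader might infer that people who stop coming are simply not counted. The document does not support that as a flat statement: it holds only if the 80% rule is the sole criterion. But the additive reading is not stated either, and under it full attenders with low completion are still counted as lost.

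It can also be said that completion over attended sessions is a legitimate measure that complements attendance, and that early stopping remains visible in the attendance rate, which uses all sessions. Both are correct. A person who stops after 8 sessions shows as 33.3% attendance. This limits the harm but does not correct the attrition figure.

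Two further inferences should be resisted. A reader might conclude that low completers will be removed from the intention-to-treat analysis. The Statistical analysis section plans both intention-to-treat and per-protocol analyses and nowhere ties the former to attrition. Its per-protocol threshold uses an attention rate, a term not defined in the article, so it does not settle the attrition rule either. A reader might also conclude that attrition could be reported as 0% or 100%, or that the main trial would lose a calculable amount of power. Those are logical limits or results of assumed behaviour. As shown above, the two errors can also offset each other.

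Finally, the article reports attrition descriptively and attaches no progression threshold to it. That is fair, and it bears on urgency, not on whether the definition is sound.

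**Conclusion.** The point holds in a limited form. One section gives two definitions of attrition that do not agree, for a component of a primary outcome. The certain consequence is over-counting: a retained and assessed participant with 19 of 24 sessions completed is attrition. The conditional consequence, if the 80% rule is the working criterion, is that people who leave early after completing what they attended are missed and never-attenders cannot be classified. The reported rate would then not measure the loss that the 20% allowance is meant to cover.

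The number of participants affected cannot be derived from the document. The 10%, 33.3% and 43.3% above rest on an assumed mix and show only that the readings can differ widely. The classification of single participants needs no assumption beyond the 24 sessions and the stated rule. Because this decides how a primary outcome is counted, it should be settled before the data are analysed.

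**What to change.** 1. Delete the sentence that equates completion below 80% with attrition.
2. Define attrition as randomised participants who withdraw or have no post-intervention assessment, divided by the number randomised, reported by arm. This gives a figure that can be compared with the 20% allowance.
3. Report low session completion separately as adherence, next to attendance over all 24 sessions.
4. Optional: add an adherence measure with all scheduled sessions as denominator, scoring 0 for those who never attend. It is not essential, since attendance is already reported over all sessions.

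The cost is slight rewording and no additional data. The trade-off is that the completion measure no longer feeds into attrition, so poor engagement within sessions has to be read from the adherence figures.

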**Methods and analysis:**

A two-arm pilot randomised controlled trial will be conducted to assess the feasibility, acceptability and preliminary effects of an MBPE program among community-dwelling older people with sarcopenia. A total of 60 participants will be randomised into the intervention group, receiving the MBPE intervention twice a week over 12 weeks, or the control group, receiving health education with the same duration, number of sessions and frequency as the intervention group. Each session of the MBPE program will last about 60 min, including 5-10- min introduction, 20-min MBI, 30-min PE and 5-10-min sharing and discussion. The primary outcomes will be the feasibility (i.e., the time spent recruiting participants, the eligibility rate and the recruitment rate) and acceptability (i.e., the attendance rate, completion rate and attrition rate) of the MBPE program. The secondary outcomes will be the preliminary effects of the MBPE program on symptoms of sarcopenia, motivation for PE, psychological well-being, mindfulness level, physical activity level and quality of life. Individual interviews will be conducted to identify the strengths, limitations and therapeutic components of the intervention. The quantitative data will be analysed by generalised estimating equations. The qualitative data will be analysed by Braun and Clarke’s thematic approach.

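### The 80% completion rule makes the attrition rate, a primary outcome, measure how fully attended sessions were performed and not loss from the trial

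*Protocol article*

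**What the plan says.** The abstract lists the attrition rate among the primary outcomes, under "acceptability (i.e., the attendance rate, completion rate and attrition rate) of the MBPE program". Section 2 (Acceptability of the MBPE program) defines three rates:

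- attendance: "attendance rate (sessions attended by the participants / all sessions")
- completion: "completion rate (sessions in which participants were actually involved and at least 80% completed / all attended sessions")
- attrition: "attrition rate (number of participants dropping out / total number of participants"), reported with the reasons for discontinuing.

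It then adds a threshold: "Attrition will be considered if the completion rate is less than 80"%. It does not say whether this replaces the drop-out formula, adds to it, or explains what dropping out means.

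Section 1 (Quantitative data analysis) sets the per-protocol population by a further 80% threshold: "The attention rate >80% will be included in the PP analysis". No rate of that name is defined in the article.

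**The concern.** Attrition normally means loss from the trial: people who withdraw or are not assessed at the end. The drop-out formula fits that meaning. The 80% sentence does not, because it depends on how much of each attended session was carried out. Its denominator contains only attended sessions, so staying away cannot lower it. The rule can therefore pass someone who was hardly there and flag someone who came every time.

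A pilot trial is run partly to supply planning figures. An attrition rate that includes participants who stayed and were assessed, and that may leave out some who were almost absent, cannot be carried into the main trial's sample size as a loss rate. Because the two sentences are not reconciled, the rate can also be calculated in more than one way once the data are in.

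**Working it through.** **The plan's own figure.** The Sample size section is the only place where attrition enters a number: 25 × (1 + 0.20) = 30 per group. This reproduces. In that use, attrition stands for participants who no longer contribute to the 25 needed.

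**Inputs.** The intervention description states: "The MBPE intervention will be conducted twice a week for 12 weeks [19"]. So there are 2 × 12 = 24 scheduled sessions. Let a be the sessions attended and c the attended sessions that meet the completion requirement.

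- Attendance = a / 24
- Completion = c / a
- Flagged as attrition by the 80% sentence if c / a < 0.80

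**Results.**

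| Attended (a) | Completed (c) | Attendance | Completion | Flagged by the 80% rule |
|---|---|---|---|---|
| 1 | 1 | 1/24 = 4.2% | 1/1 = 100% | no |
| 2 | 2 | 2/24 = 8.3% | 2/2 = 100% | no |
| 5 | 4 | 5/24 = 20.8% | 4/5 = 80% | no |
| 24 | 20 | 24/24 = 100% | 20/24 = 83.3% | no |
| 24 | 19 | 24/24 = 100% | 19/24 = 79.2% | yes |
| 0 | 0 | 0% | 0/0 | undefined |

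A participant with one completed session can pass the rule while one with 19 fails it.

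**Would a different denominator cure it?** Using c / 24, the participant with 2 attended and 2 completed falls from 100% to 2/24 = 8.3% and is flagged. The participant with 24 attended and 19 completed stays at 79.2% and is still flagged despite full attendance. Changing the denominator cures only one side, so attrition and adherence have to be separated.

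**Size.** One participant classed differently moves the rate by 1/30 = 3.3 points in one arm, or 1/60 = 1.7 points overall. The article gives no basis for predicting how many there will be. As an assumed range for one arm, 1, 3 or 6 participants give 3.3, 10 or 20 points. Six would equal the whole 20% planning assumption (6/30).

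**Per-protocol rule.** If the undefined rate means attendance, the participant with 24 attended and 19 completed is included (100%) and the one with 2 attended and 2 completed is not (8.3%). If it means completion, the two change places (79.2% and 100%). With attendance, above 80% means more than 0.80 × 24 = 19.2, so at least 20 sessions.

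**The case against.** The strongest reply is that there is only one definition: the formula gives the rate, and the threshold says who counts as having dropped out. That is a possible reading, though the article does not state it. It does not help, because the completion rule would then govern the primary outcome in full and the reversal above would apply directly.

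Other parts of the reply stand:

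- A near-absent participant who withdraws is counted by the drop-out formula. It would be too strong to infer that such people are always retained. Likewise, only full attenders with 19 or fewer completed sessions are flagged, not full attenders in general.
- Completion over attended sessions is a legitimate measure beside attendance: one shows whether people come, the other whether they finish once there. Its denominator is a problem only because it drives attrition. The attendance rate is properly defined and unaffected.
- The undefined term in the per-protocol rule is most likely a slip for attendance. It needs correcting, but the completion reading is the less likely one.
- Acceptability is reported as rates or counts, and the article ties no test or progression threshold to attrition. Reasons for discontinuing are collected, so drop-out and non-adherence could still be reported apart.

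**Conclusion.** The point holds in limited form. As written, the 80% sentence lets non-adherence count as attrition and can reverse the classification of participants: 2 of 2 sessions gives 100% and no flag, while 19 of 24 gives 79.2% and a flag. This affects a reported primary outcome and its use in planning the main trial, by 3.3 points per participant in an arm of 30. It rests on 24 scheduled sessions, derived from the stated frequency and duration, and on applying the sentence literally. The number of participants affected is unknown.

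A reader might infer that the intention-to-treat analysis is compromised. The article does not support that: nothing says that participants below 80% are removed or left unassessed, and outcomes are scheduled at baseline and after the intervention without restriction. Nor can it be said that the observed rate is certain to be incomparable with the cited 20%, because the source's definition of attrition is not shown. The point should be fixed; it is not a fatal defect.

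**What to change.** In section 2 (Acceptability of the MBPE program), delete the sentence that ties attrition to completion below 80%. Define attrition once: randomised participants who withdraw or have no post-intervention assessment, divided by all randomised, reported by arm. Report attendance and completion separately as measures of adherence. Completion may stay over attended sessions once it no longer determines attrition.

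In section 1 (Quantitative data analysis), replace the undefined rate in the per-protocol rule with the defined attendance rate, and state that above 80% means at least 20 of 24 sessions.

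The cost is wording only. No extra data, participants or visits are needed beyond what the article already plans.
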